### 2.1. Data Collection

Study participant demographic data (age, nationality, body mass index (BMI), parity, weeks of gestation, type of UI, and severity) will be recorded on the first day of enrolment into the study. The UI will be assessed via the International Consultation on Incontinence Questionnaire—Urinary Incontinence Short Form (ICIQ-UI SF) [29,30] (Table 1). 

The Technology Acceptance Model (TAM) framework will be used to assess the acceptability of the KEPT-app. According to TAM, the questions assess the complexity, content, and comfort [43], for example, (1) How many stars would you use to recommend this app to your friends? (2) How many stars would you rate the content of this app? (3) How many stars would you rate the comfort using this app? (4) Do you find it complex using this app?

The Malay-mHealth App Usability Questionnaire (M-MAUQ) will be used [46,50] to evaluate the feasibility and usability of the app. This questionnaire will assess the ease of use, interface, satisfaction, and mHealth app usefulness to the study participants. 

The study participants will assess their knowledge, attitude and practices toward PFMT to evaluate any improvement after the intervention [53]. For assessing the self-efficacy and adherence towards PFMT, the Exercise Adherence Rating Scale (EARS) [51] and Self-Efficacy Scale For Practicing Pelvic Floor Exercise Questionnaire (SESPPFE) [52] will be used. Additionally, cost efficiency will be assessed as explained in the study protocol published elsewhere using the quality of life of the study participants [26]. The Patient Educational Material Assessment Tool (PEMAT) will be used to validate the educational video embedded in the app [47].

Responses from the open-ended questions will be analysed further to understand the study feasibility and app acceptability. The participants’ information regarding the recruitment and study process will be assessed, and study process improvement will be taken for the future definitive KEPT-app trial. The consensus of the participants’ technical findings will inform the developer in improving the technical part of the app.

In evaluating the cost analysis study, the data from the two-month follow-up will be extrapolated to one year for the calculations. We will collect each participant’s training time; incontinence aids, for example absorbent pads; and laundry (if applicable) at baseline and at a two-month follow-up among all the participants [54]. We will utilise the International Consultation on Incontinence Modular Questionnaire on Lower Urinary Tract Symptoms and Quality of Life to measure their quality of life to calculate the quality-adjusted life years (QALYs) gained [54].

### 2.2. Statistical Analysis

The primary analysis of this pilot study will be by descriptive analysis to concentrate on the feasibility outcomes. The recruitment number and the proportion of participants screened, consented, and randomised will be presented. Additionally, the information of the dropouts will be presented with their reasons in the results.

The results of study outcomes and validation of educational video will be analysed. Exploratory analysis of the effect sizes for PFMT adherence will be conducted by mixed-effects regression analyses, controlling for significant baseline characteristics, such as age, parity, educational status, and income status. For the cost-effectiveness analysis, expenditures during the study will be compared between the groups using the multiway sensitivity analysis.

As the data will be sent via the app, the system will collect the data and store it in a secured and encrypted cloud storage. The researcher (blinded) who has been trained with a statistical analysis program will analyse the data using the Statistical Package for the Social Sciences version 27.0, IBM, New York, United States of America [55,56].

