## 2. Materials and Methods

Design overview: This pilot study will use a single-blind, single-centre, parallel, randomised controlled trial (RCT) design that will incorporate individualized treatment flexibility, as in a real-world setting, and provide the future study’s feasibility process [26]. The study protocol was designed and reported according to CONSORT (Consolidated Standards of Reporting Trials) extension for randomised pilot and feasibility trials [27,28].

Participants (eligibility criteria): The eligible participants are: (1) pregnant women aged over 18 years old, (2) any parity at 26–27 weeks’ gestation, (3) with either stress UI or mixed UI according to the International Consultation on Incontinence Questionnaire—UI Short Form [29,30], and (4) Malaysian citizens. Other citizens will be excluded as the primary language used in this study will be Malay, the national language of Malaysia.

Additionally, pregnant women with chronic medical problem(s) before pregnancy, complicated pregnancies, or conditions with which it is not advisable to practise PFMT will be excluded.

Recruitment and withdrawal: This study will be conducted at one primary care clinic in the Hulu Langat district under the same management as the future study [26]. The recruitment process will follow the future study, whereby pregnant women will be invited from a poster announcement [26]. They will then contact the research assistant (RA) via WhatsApp or Short Message System (SMS) for the eligibility screening process. Once a pregnant woman is eligible to join the study, the RA will provide her with a link to download the app for the consent forms. (Figure 1)

All study participants can withdraw at any time during the trial with or without any reasons. The RA will contact those who have withdrawn to obtain reasons and their experiences joining this pilot study. This finding will be analysed and given as input into the barriers that will add to future study modifications.

For the sample size, an analysis suggested that 12 participants per group is an appropriate sample in a feasibility study [31] and another review stated that 15 participants per group could be adequate for moderate effect sizes [32]. A pilot randomised controlled trial for an expected small effect size should have 25 participants per arm [33]. However, considering a possible 20% dropout rate, the final sample size will be 64 participants with 32 participants per arm.

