The KEPT-app feasibility will be defined as KEPT-app’s extent of successfully being used or carried out in a primary care clinic setting [45]. The app feasibility will be assessed along with the usability assessment, which can assess the ease of use, interface, satisfaction, and mHealth app usefulness [46]. Additionally, the PFMT education video embedded in the app should assess its understandability and actionability [47]. 

Secondary outcomes are as follows; (1) feasibility of recruiting the study participants, which include numbers and proportions of participants recruited, screened, consented, and numbers with their reasons for withdrawals; (2) face validation on the educational video embedded in the app; (3) appropriate training time in achieving the advanced skill level; (4) control group’s barriers continuing the study; (5) barriers and suggestions for using the app; (6) the knowledge, attitude, and practice of PFMT; and (7) quality of life.

Training time will be recorded automatically via the app and a reminder will be delivered (during the evening) if no PFMT is recorded on that day. There will be three training skills: beginner (2 s each contraction), intermediate (6 s each contraction), and (10 s each contraction). The pregnant women are scheduled for ten repetitions each set and must complete three sets every day. The time recorded will be analysed using the algorithm to measure which training skills will change their self-efficacy and adherence.

It is essential to determine the KEPT-app’s preliminary effectiveness to improve the PFMT skills of pregnant women. The time recorded by the pregnant women will be analysed with the self-efficacy improvements and adherence towards PFMT. Additionally, the recorded time will be analysed with the UI changes within the group.

Additional qualitative data collection will be used to further understand any barriers or suggestions from the study participants. The expenditures during the study, for example, the cost of absorbent pads, participant’s salary, and cost of laundry where applicable, will be compared between the groups to assess the cost-effectiveness.

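### The one method named for comparing costs between the arms, a multiway sensitivity analysis, does not in its ordinary form show sampling error; the mean cost difference needs an interval beside it

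*Protocol article*

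**What the plan says.** The protocol article commits, at the end of its Introduction, to a cost-effectiveness analysis from the societal perspective. The only sentence on how the arms will be compared is in section 2.2 (Statistical Analysis): "expenditures during the study will be compared between the groups using the multiway sensitivity analysis".

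Other places bear on it:

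- Section 2 (Materials and Methods) lists "the cost of absorbent pads, participant’s salary, and cost of laundry where applicable" as examples of expenditure and says that these "will be compared between the groups to assess the cost-effectiveness". It names no method.
- Section 2.1 (Data Collection) has training time, incontinence aids and laundry recorded for each woman at baseline and two months. It adds that "the data from the two-month follow-up will be extrapolated to one year for the calculations" and that a quality-of-life questionnaire will be used "to calculate the quality-adjusted life years (QALYs) gained". It names no way of comparing the arms.
- Section 2.1 also refers the assessment of cost efficiency to the earlier published protocol, which is not at hand.
- The mixed-effects regression in section 2.2 is stated for adherence to the exercises, not for costs.

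**The concern.** The sentence sets a task, comparing expenditure between two randomised groups, and assigns a tool that answers a different question. A deterministic multiway analysis takes the observed mean use of each item in each arm as given and varies unit costs and other assumptions jointly. Woman-to-woman variation does not enter, so the resulting range is not an interval for the cost difference.

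This is more than detail left to an analysis plan, because the article does name a method, and a plan that followed the sentence literally would inherit the gap. In a trial of this size, sampling error is likely to be a large part of the uncertainty about costs. A reader shown only a sensitivity range could take a chance difference for a stable one. Extrapolating two-month data to a year would enlarge that difference without showing its error.

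**Working it through.** **1. Sample size.** Section 2 states that "A pilot randomised controlled trial for an expected small effect size should have 25 participants per arm" and then, "considering a possible 20% dropout rate", arrives at 32 per arm. This is reproduced: 25 / (1 − 0.20) = 31.25, rounded up to 32 per arm and 64 in total. The cost comparison will therefore rest on about 25 to 32 women per arm. The article states no figure for the cost analysis itself.

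**2. Sampling error of a mean cost difference.** The standard error is SD × √(2/n). The 95% half-width, with a t value of about 2.01, is:

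- n = 25: 2.01 × √(2/25) = 2.01 × 0.283 = 0.57 SD
- n = 32: 2.01 × √(2/32) = 2.01 × 0.25 = 0.50 SD

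With 1.96 in place of 2.01 the values are 0.55 and 0.49 SD. The article gives no cost SD, so the size relative to mean cost is shown over an assumed range of the coefficient of variation (CV), using 1.96:

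| Assumed CV of cost | Half-width, 25 per arm | Half-width, 32 per arm | Median absolute chance difference, 25 per arm |
|---|---|---|---|
| 0.5 | 28% of mean | 25% | 10% |
| 1.0 | 55% | 49% | 19% |
| 1.5 | 83% | 74% | 29% |

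**3. What a multiway range measures.** Let d_k be the observed difference between arms in mean cost for item k, and let each unit cost be multiplied by a factor m_k between 1 − s and 1 + s. The total difference is D = Σ m_k d_k. Its extremes over the range are Σ d_k ± s Σ|d_k|. The sign is therefore kept throughout exactly when |Σ d_k| > s Σ|d_k|. Neither the variance between women nor the sample size appears in that condition.

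**4. How often a chance difference keeps its sign.** The simulation used no true difference, 25 or 32 women per arm, and 2,000 trials per setting. Assumptions, none of them in the article:

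- three or four cost items (sections 2 and 2.1 together name pads or aids, laundry, salary and training time)
- log-normal costs with CV 1
- correlation 0 or 0.3 between items
- cost shares either equal or dominated by one item at 70%
- all unit costs moved jointly to every corner of the range

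| Unit-cost range | Sign kept at every corner | Sign kept and 95% interval includes zero |
|---|---|---|
| ±10% | 89-96% of trials | 85-92% |
| ±20% | 77-93% | 73-89% |
| ±30% | 67-88% | 62-83% |
| ±50% | 46-79% | 42-75% |

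Over the same settings a 95% interval for the mean difference excluded zero in about 3-6% of trials. As step 3 implies, the sign-keeping figure hardly depends on n. With three equal uncorrelated items at ±20% it was 83% at 25 per arm (0.8315) and 84% at 32 (0.837). The lowest figures, about 46-47%, came from four equal uncorrelated items at ±50%.

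**The case against.** The strongest objection is that the article condenses a method set out elsewhere. Section 2.1 points to the earlier protocol for cost efficiency, and that document may specify an interval or a bootstrap. A reader might infer that no valid cost comparison is planned; the article does not support that. What stands is narrower: section 2.2 states its own method for this pilot's between-group comparison, and as worded that method does not do the job.

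Second, the article does not say whether the analysis is deterministic or probabilistic, or which ranges apply. A probabilistic version built on the sampled costs, or ranges taken from their spread, would carry sampling variation. The deterministic reading is the ordinary one but remains an inference. If something else was meant, the sentence still needs to say so.

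Third, the simulated percentages depend on assumptions, and the rule that an unchanged sign counts as robust is not the article's. A reader might infer that a chance difference would always, or nearly always, survive the sensitivity range. That holds by algebra for a single cost item, but this trial names three or four, and with wide ranges the share can fall below half. The simulation also varied unit costs only, not the extrapolation to one year.

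Fourth, a reader might infer that a chance saving would pass into the future trial's economic result. No section says that pilot costs will be used there. The stated uses are feasibility, barriers and changes to the design.

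Finally, the primary analysis is descriptive, section 2 says that this is not an effectiveness study, and cost appears neither among the numbered secondary outcomes nor in Table 1. No decision rule rests on cost. This limits the severity.

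**Conclusion.** The point holds in a limited form. The only between-group method for costs named in this article shows, in its ordinary form, dependence on assumed inputs and not sampling error. The half-width of about 0.50 SD (32 per arm) to 0.57 SD (25 per arm) follows from the planned numbers alone. That a chance difference can keep its sign across the whole range follows from the algebra. How often it does so, about 77-93% at ±20% and 46-79% at ±50%, rests on the assumed distributions, item shares and ranges, and is an illustration rather than a property of this trial.

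The unseen earlier protocol may already supply an interval. With costs ancillary in a descriptive pilot of 64 women, severity is moderate to minor: the sentence should be corrected, but the main feasibility aims are not affected.

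**What to change.** Replace the sentence in section 2.2 with wording to this effect: *Mean expenditure per woman will be compared between the randomised groups as a mean difference with a bootstrap 95% confidence interval, resampling women within arm. Costs and QALYs will be resampled together to give the uncertainty of the incremental results. A multiway sensitivity analysis will be reported as a supplement, to show dependence on unit costs and on the extrapolation to one year.* Resampling within gravida strata, to match the randomisation, is an optional refinement. If the earlier protocol already specifies such an interval, a cross-reference at this point would be enough.

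The bootstrap does not settle whether two-month data can stand for a year, which is why the sensitivity analysis should stay.

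The cost is a sentence or two of wording and a short computation on data already to be collected, with no extra women, visits or questionnaires. The downside is that the cost result will look less certain, which is a fair picture at 25 to 32 women per arm.

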Perceived usefulness refers to “the degree to which a person believes that using a particular system would enhance his or her job performance” and perceived ease of use indicates “the degree to which a person believes that using a particularly stem would be free of effort” [40]. Meta-analysis highlighted that perceived usefulness is the most common predictor of mHealth use and showed a medium-strength relationship with perceived ease of use [41]. Therefore, the mHealth app with a simple design will encourage the users to use it, and their perception of effortless use the app will motivate them to continue using the app. The relationship between Technology Acceptance Model (TAM), Persuasive Technology, and COM-B model is illustrated in Figure 2.

The KEPT-app, developed for the Android version 9.0 operating system, consists of the following main user interfaces: (1) the main login page, (2) the PFMT training video, (3) the exercise module with a timer, (4) a calendar for users to chart their wet days and completed exercise, and (5) a score board. At the time of writing, the KEPT-app prototype is undergoing usability evaluation by both the experts in informative technology and health informatics and from the end-users (pregnant women with UI). Feedback from the usability evaluation will be used to revise the app. The final KEPT-app will then be tested during this feasibility study. The app will be delivered only to the study participants and not through the official stores.

The control group will receive antenatal care as usual during the intervention period and access to install the app after 36 weeks of pregnancy. Routine antenatal care follow-up will be based on the Ministry of Health guidelines [42]. 

Primary outcomes are the outcomes relevant to the acceptability of the KEPT-app. Acceptability and feasibility of the KEPT-app is the satisfaction and agreeableness of the app’s pregnant women [43]. Acceptability is crucial as it affects the success of an implementation phase [44]. The acceptability will be assessed for its content, complexity, and comfort [43]. 

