Trial feasibility (treatment fidelity) is crucial to ensure that PFMT is performed by the participants according to the system log recorded. The monitoring must be continuously performed to ensure the treatment fidelity. Treatment fidelity describes “the methodological strategies used to monitor and enhance the reliability and validity of behavioural interventions” [48]. Therefore, the RA must actively monitor the system log activities (training time) and immediately inform the researcher if any system failure or no activities are recorded by the patients.

The adherence to the training time is when the pregnant women complete 80% of the expected training time, which will be continuously recorded after they watch the video [49]. The calendar apps method will record their PFMT, and if they have not logged the data, a reminder will be delivered automatically. The adherence rate data will inform future studies when the best time is to send the booster or reminders. Any errors or issues will be recorded, and the system update or debugging will be recorded for further analysis.

To assess the trial feasibility of the recruitment of study participants and retention rates, the total number of study participants who can be recruited, screened, and interested in participating within one month will be examined. The researchers will assess the study feasibility by reviewing the timing log data recorded during the pilot study. This recruitment process is critical as there will be no researcher on-site to promote this study due to the uncertainty of the restricted movement due to the COVID-19 pandemic. 

Any dropout or defaulter will be traced and contacted. The number of withdrawals will be recorded and descriptively analysed. There will be no further analysis for the dropouts with per-protocol (PP) analysis and intention-to-treat (ITT) analysis to evaluate the influence of missing data as this is not an effectiveness study.

We will perform primary and secondary outcome measures at three time points during the trial to assess the trial feasibility in collection of outcome data—at enrolment into the study, a baseline assessment will be recorded, and one-month and two-months post-intervention, an assessment will be recorded accordingly for both groups.

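### Study data are sent through the app under test, and no other route is stated for the scored outcomes of women who delete it or cannot use it

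*Protocol article*

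**What the plan says.** Section 2.2 (Statistical Analysis) of the protocol article gives one route for data: "As the data will be sent via the app, the system will collect the data". It does not list which data this covers, and the article names no second route for questionnaires.

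Section 2 (Materials and Methods) defines what is measured first: "Primary outcomes are the outcomes relevant to the acceptability of the KEPT-app". Section 2.1 and Table 1 score this by star ratings and the M-MAUQ. The ICIQ-UI SF, EARS and SESPPFE are among the secondary measures. On timing, section 2 says that after baseline, at "one-month and two-months post-intervention, an assessment will be recorded accordingly for both groups".

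For women who leave, section 2 says: "The RA will contact those who have withdrawn to obtain reasons and their experiences joining this pilot study". It adds that dropouts and defaulters will be traced and contacted, without saying what is collected then. Qualitative feedback on barriers is gathered after the study ends. The section also declines any further per-protocol or intention-to-treat analysis of how missing data affect the results, on the ground that this is not an effectiveness study.

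A contact channel outside the app exists from the start. Of women who respond to the poster, section 2 says: "They will then contact the research assistant (RA) via WhatsApp or Short Message System (SMS) for the eligibility screening process".

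**The concern.** The object being rated is also the stated instrument for collecting the rating. A woman who found the app hard to use, met a fault or removed it is likely to rate it low, and she is also the woman least able to answer through it. Missing scores would then depend on the primary outcome itself. No later analysis can restore ratings that were never captured, and the article rules out examining the influence of missing data.

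Two results are at stake. The first is the scored acceptability and usability of the app, which would look better than it is if stoppers like it less. The second is what the pilot can tell the main trial about collecting outcome data. If questionnaire return is not reported separately from app use, a low return rate is hard to interpret. The app arm's incontinence, adherence and self-efficacy scores could be lost in the same way, though the direction of any bias there is less clear.

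**Working it through.** **1. The plan's own figure.** Section 2 states "A pilot randomised controlled trial for an expected small effect size should have 25 participants per arm" and then "considering a possible 20% dropout rate, the final sample size will be 64 participants with 32 participants per arm". Inflating 25 for 20% dropout gives 25 / (1 − 0.20) = 31.25, rounded up to 32 per arm and 64 in total. The figure reproduces, and nothing in this point changes it.

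**2. What each planned safeguard is stated to supply for a woman who no longer has a working app.**

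- Contact with withdrawn women (section 2): reasons and experiences. Scored instruments are not mentioned.
- Tracing of dropouts and defaulters (section 2): contact, with content not stated.
- Log monitoring and automatic reminders (section 2): these are triggered by system failure, or by training that is absent or not logged. They are not described as chasing questionnaires.
- Qualitative feedback after the study ends (section 2): barriers and suggestions, so narrative rather than scores. How it reaches women who stopped is not stated.
- Reporting of dropouts with reasons (section 2.2): counts and reasons.

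None of these is stated to yield star ratings, M-MAUQ, ICIQ-UI SF, EARS or SESPPFE scores.

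**3. Illustration of size, in stars.** The documents give no app-abandonment rate and no expected rating. The 20% in section 2 is study dropout and is borrowed here only as a scale: 0.20 × 32 = 6.4, taken as 6 women not responding and 26 responding. Assume a mean of 4.2 stars in responders, 2 to 3 stars in the others had they answered, and no response from any of the 6.

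Overstatement = (share not responding) × (mean in responders − mean in non-responders)

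- Non-responders at 2 stars: 6/32 × (4.2 − 2.0) = 0.1875 × 2.2 = 0.41. The mean over all 32 is 3.79.
- Non-responders at 3 stars: 6/32 × (4.2 − 3.0) = 0.1875 × 1.2 = 0.225, about 0.23. The mean over all 32 is 3.975.

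Range over the assumed number not responding:

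- 3 of 32: 0.11 to 0.21 stars
- 10 of 32: 0.38 to 0.69 stars
- 13 of 32: 0.49 to 0.89 stars

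**4. The same as a proportion.** Assume that 80% of responders rate the app favourably. With 6 of 32 missing, the overstatement is 0.1875 × (80% − favourable share in non-responders):

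- 60% favourable: 3.8 points
- 40% favourable: 7.5 points
- 20% favourable: 11.3 points
- 0% favourable: 15.0 points

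With no assumption about the 6, the favourable share among all 32 lies between 26 × 0.80 / 32 = 65.0% and (26 × 0.80 + 6) / 32 = 83.8%. If non-responders felt as responders do, the bias is zero.

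**The case against.** The strongest reply is that one sentence about transmission and storage does not make questionnaires depend on continued app use. The app's main interfaces listed in section 2 are login, video, timed exercise module, calendar and score board, with no questionnaire module, so the sentence might refer mainly to training and calendar logs.

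The control arm points the same way. Controls enter at 26–27 weeks and may install the app only after 36 weeks, yet both arms are assessed at one and two months. Controls must therefore answer outside the app, or through the copy downloaded for the consent form. On either reading, answering can be separated from using the intervention. It can also be said that a journal article leaves questionnaire logistics to the full protocol.

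Much of this stands. It defeats three stronger conclusions that a reader might draw:

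- **That a woman who stops using the app thereby stops supplying outcomes.** She may stop training and still answer; only deletion or a disabling fault blocks the channel.
- **That the acceptability result comes only from continuing users.** Defaulters are traced with no stated limit on what is collected, and narrative feedback is planned.
- **That app non-use and study dropout become the same event.** Training logs, withdrawal counts and recorded reasons can partly separate the two.

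The objection does not remove the stated choice. Section 2.2 says without qualification that the data travel by the app, and the primary outcome is a rating of that app. The reading limited to logs is possible, but the text does not say so. The control-arm wording adds a reason to state the route for both arms.

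**Conclusion.** The point holds in a limited form. The article sends data through the intervention, states no other route for scored outcomes once the app is deleted or unusable, and plans no look at the influence of missing data. The scored primary result therefore risks resting mainly on continuing users, with an upward bias if those who stop like the app less.

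The size is unknown. The illustration of 0.23 to 0.41 stars rests on assumed ratings, on 6 of 32 women not responding and on none of them being reached another way. It shows scale and is not an estimate. The documents give no acceptability threshold against which to judge it. The change is still worth making before recruitment, because it is cheap and ratings that are not collected cannot be recovered.

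**What to change.** - State the route for the questionnaires in each arm. Make the one- and two-month questionnaires available to all randomised women whether or not the app is installed or used, for example by a secure web-form link or a phone call through the WhatsApp/SMS contact the research assistant already has.
- When dropouts and defaulters are traced, ask those who are willing for the scored ratings as well as reasons: star ratings and M-MAUQ in the app arm, and the other instruments as due.
- Report responders out of all allocated, by arm and visit, separately from app discontinuation. For the app-arm acceptability result, add simple best-case and worst-case bounds over all allocated women.

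The cost is one online form, a few messages per woman and the linking of form identifiers to app identifiers. Sample size, treatment and visit schedule do not change. A web link may also miss some disengaged women, so the response counts are needed in any case.
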